### ***Primary Outcome measures***

- cure rates at end of treatment (6 months). A cure is defined as one negative sputum culture in patients who did not fail treatment. A treatment failure is defined as:

1. a patient who is persistently smear positive by five months of treatment
2. a patient who becomes smear negative but positive again at or after five months of treatment (note: sputum positivity before this time is not considered a treatment failure)

- ***Secondary outcome measures***
- early response rates: proportion of patients with negative culture results at 8 weeks after initiation of therapy
- proportion of patients with relapses during the 72 weeks follow up period after the end of treatment. A relapse is a patient previously treated for tuberculosis who has met the case definition of cure (as defined above) and been declared cured by a physician and who has now been diagnosed with bacteriologically positive (two positive smears and culture positive) tuberculosis. If there is discordance between smear and culture results, a clinical decision will be made regarding further management: (i) smear positive, culture negative, and (ii) smear negative and culture positive.
- cure rates in HIV positive TB patients
- proportion of patients with clinical deterioration of pulmonary tuberculosis with the need for hospitalisation
- proportion of patients with *serious* adverse events any time during chemotherapy
- proportion of patients with any adverse events during chemotherapy
- proportion of patients completing treatment (defined as patients who achieved a total of 54 out of 56 doses in the first eight weeks of treatment AND 107 out of 112 doses at a daily rate during the subsequent 16 weeks of treatment) within each group. (96% doses taken considered as completed in intensive and maintenance phases).
- Proportion of patients who developed MDR-TB

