**3.6 Study conduct**

The flow of patients is illustrated in the flow chart (Annex ). Patients will be seen by the clinic physicians as per the clinic routine. From this consultation, any smear positive cases of pulmonary TB will be referred to the research team to assess eligibility. Consenting patients will undergo full assessment as detailed in the CRF. This will include: (i) sputum culture, (ii) HIV counselling and testing (including CD4 count), (iii) a full blood count, (iv) liver function tests (SGOT, SGPT, alkaline phosphatase, direct and total bilirubin, albumin), fasting blood sugar (v) renal function tests (creatinine, blood urea nitrogen), and (vi) a urinary pregnancy test, uric acid and urinary glucose, protein, bilirubin and urobilinogen.

Sputum specimens for direct smear will be collected on Day 0, Weeks 8, 20, and 24 (See table). At each of these times three sputum specimens will be provided: after deep cough: one spot, one morning and a second spot specimen. A patient is considered smear negative if: (i) all 3 consecutive sputum smears are read as negative, or (ii) 4 out of 5 are read as negative in the event that only two of the first three smears was negative. (Note: with TB co-infected HIV patients, more patients are smear negative).

Culture will be done on Day 0 and weeks 8 and 24. A culture and sensitivity at week 20 will only be done if sputum samples of the same week are positive. Sensitivity test on the stored sputum samples from week 0 will also be done if sputum samples at week 20 are positive. A minimum of three sputum samples will be required from each patient at each of these time points. Sample collection will be done on days when patients come to collect their drugs. Cultures will be inoculated from pooled sputum samples.

For the purpose of defining the cure and relapse rates, only the sputum culture result will be used. Standard operating procedures have been prepared for collection, storage, transport, and testing of culture samples before the study starts.

Time frame for the duration of the study:

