**Enrolment** **Week 8 Week 20 Week 24**

Time zero (End of intensive phase) (End of continuation phase)

(follow up period starts )

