**Week 36 Week 48 Week72 Week 96**

(End of trial)

| Study procedures | Screening | Enrolment  Study Drug  T=0h | Week 8  (end of intensive phase) | Week  20 | Week 24  (end of continuation phase) | (Weeks 36,48,72 and 96) |
| --- | --- | --- | --- | --- | --- | --- |
| Medical History | X |  |  |  |  |  |
| Physical Examination | X |  | X | X | X | X |
| Sputum for AFB smear | X |  | X | X | X | X |
| Sputum for culture |  | X | X | Xa | X | Xa |
| Sensitivity testing |  |  |  | Xb |  |  |
| Informed consent | X |  |  |  |  |  |
| Haematology and Clinical chemistry | X | X | X | X | X | X |
| Urine analysis | X | X |  |  |  |  |
| Pregnancy test | X |  |  |  |  |  |
| HIV testing  CD4 test | X  Xd |  |  |  | Xd | Xd |
| Randomisation |  | X |  |  |  |  |
| Drug administration |  | X | X | X | Xe |  |
| Adverse Events |  | Symptom checklist | X | X | X | X |

Xa It the sputum smear is positive

Xb Sensitivity testing of screening smear and 5 month smear if sputum is positive.

Xd CD4 testing only for HIV positive TB patients. Repeat CD4 test on weeks 24, 48, 72 and 96. Not indicated at week 36.

Xe By the end of week 24, treatment should be completed.

Patients will be instructed to attend the TB treatment centre, for the duration of treatment; both the intensive and maintenance phases. All drug doses will be administered under observation and documented by the trial nurse. All drug doses in the continuation phase will be administered under standard operation of DOTS of the country. Patients will also be evaluated for clinical, haematological and biochemical parameters during these follow up period.

Trial subjects will be followed up for 72 weeks after the completion of treatment. They will be required to come to TB treatment centre for clinical, haematological and biochemical assessments at the end of 36 weeks ,48 weeks ,72 weeks and 96 weeks after initiation of treatment. A home visitor will trace individuals who fail to come at the specified time points. At each follow-up time, subjects will provide three sputum samples: one spot, one morning and a second spot sputum specimens for smear examination at each of the three follow up visits. Cultures will be done only for smear positive individuals (as defined above).

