## 6.4 Data analysis

The database file generated thus will be converted into statistical package STATA software version 7 (STATA Corporation, Texas, USA) and analysed by the study statistician, and PI in collaboration with the study director. Analysis will be both (a) by intention-to-treat, and (b) per protocol (excluding those who did not receive adequate chemotherapy or were withdrawn from the study), including survival analysis.Subjects will be compared based on their assigned treatment using chi-square, Student's t-test or the Wilcoxon rank sum test as appropriate depending on the scale of measurement and the validity of underlying assumptions for the baseline characteristics. Primary and secondary outcomes for each study subject will be recorded as positive (desirable) and negative (not desirable) at a pre-specified time. For primary outcome Chi-square will be used to compare proportions of culture positive and culture negative subjects at the end of the study in the two treatment groups. The effects of confounding variables (such as age and sex) will be adjusted using multiple logistic regression. In model construction, backward elimination will be employed using important independent variables initially. An alpha of 0.10 will set the significance level for entering a variable into the model. Chi-square will also be used to compare differences in each of the three secondary end points. In the whole analysis, an alpha of 0.05 will set the significance level for testing the null hypothesis. In presenting results exact p-value as obtained from the computer program will be presented.

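### Section 6.4 sets the primary test at the end of the study, but the primary outcome is cure at the end of treatment (week 24), the last visit at which every patient is cultured

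*Protocol*

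**What the plan says.** **Primary outcome (section 2.2, Primary Outcome measures).** The outcome is "cure rates at end of treatment (6 months). A cure is defined as one negative sputum culture in patients who did not fail treatment". Failure is defined by smear: either persistently positive by month five, or positive again at or after month five.

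**Primary test (section 6.4).** For the primary outcome, a chi-square test will "compare proportions of culture positive and culture negative subjects at the end of the study in the two treatment groups". The sentence before it says that each subject's outcomes are recorded as desirable or not at a time fixed in advance, but names no time. The section also promises both intention-to-treat and per-protocol analyses.

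**Timeline and cultures (section 3.6).** Under the heading "Time frame for the duration of the study", the line runs from enrolment to week 96. Week 24 is the end of the continuation phase, annotated "follow up period starts", and week 96 is labelled as the end of the trial. Culture is scheduled for all patients on day 0 and at weeks 8 and 24. For the visits at weeks 36, 48, 72 and 96 the text reads "Cultures will be done only for smear positive individuals (as defined above"), and the footnote to the procedures table agrees.

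**Definition of cure (section 3.6).** The same section says that the culture result alone decides cure.

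**The concern.** The sentence in section 6.4 is the only one in the protocol that states the primary comparison, and its time point does not match the outcome it is meant to test. The protocol separates the end of treatment from the end of the trial by 72 weeks, so the mismatch is more than two names for one date.

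The mismatch also bears on what data exist. At the final visit most patients, being smear negative, would have no culture. A table of culture positive against culture negative at that visit would contain only patients chosen by their smear result. That is not a comparison of the randomised groups and does not estimate cure. Anyone programming the analysis from section 6.4 alone would get something other than the primary result, or would have to guess what was meant.

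**Working it through.** **1. The plan's own figure.** Section 4 gives 498 per arm: 96% cure in the comparator group, a 4% margin, one-sided 5%, 90% power, 10% dropout. The Farrington-Manning test of two proportions (null variance by restricted maximum likelihood) has

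n = (z₀.₉₅·√V₀ + z₀.₉₀·√V₁)² / 0.04²

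- V₁ = 2 × 0.96 × 0.04 = 0.0768.
- The restricted null proportions are 0.972 and 0.932, so V₀ = 0.972 × 0.028 + 0.932 × 0.068 ≈ 0.0906.
- n = (1.645 × 0.3009 + 1.282 × 0.2771)² / 0.0016 ≈ 452.
- Dropout added as 452 × 1.10 = 497.2, rounded up, gives 498. Dividing by 0.90 gives 503.

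The figure reproduces and is not in question here. It is a calculation about the proportion cured, the outcome in section 2.2.

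**2. Dates.** Treatment is 8 + 16 = 24 weeks. Follow-up is 72 weeks after treatment. 24 + 72 = 96, the visit labelled as the end of the trial.

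**3. Who has a culture, by visit.**

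| Visit | Culture |
|---|---|
| Day 0, week 8, week 24 | All patients |
| Week 20 | Smear positive only |
| Weeks 36, 48, 72, 96 | Smear positive only |

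**4. Size on the literal reading.** With 10% dropout, 498 × 0.90 ≈ 448 per arm remain. The week-96 smear-positive rate is not in the protocol, so a range is assumed:

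| Assumed smear-positive share | Patients per arm with a week-96 culture |
|---|---|
| 1% | 448 × 0.01 ≈ 4 |
| 3% | 448 × 0.03 ≈ 13 |
| 5% | 448 × 0.05 ≈ 22 |
| 10% | 448 × 0.10 ≈ 45 |

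Whatever the rate, the cultured patients are selected by smear, so no culture proportion for the randomised groups can be formed from that visit.

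**5. Changing the date does not settle the variable.** Take a patient who is smear positive at week 20 and culture negative at week 24. Under section 2.2 this patient has failed and is not cured. Under section 3.6, where culture alone decides, and in the culture table of section 6.4, the same patient counts on the favourable side.

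**6. If patients without a week-24 culture were counted as not cured.** Suppose the 96% applies to those who remain and all of the 10% dropouts count as not cured. Expected cure is then 0.90 × 0.96 = 86.4%. With unpooled variance and one-sided 5%:

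- SE at 498 per arm = √(2 × 0.864 × 0.136 / 498) = 0.0217.
- Power = Φ(0.04/0.0217 − 1.645) = Φ(0.196) ≈ 58%.
- For 90% power: n = 0.2350 × (1.645 + 1.282)² / 0.0016 ≈ 1,258 per arm.

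**The case against.** **Loose wording.** The best defence is that the phrase in section 6.4 simply means the end of treatment. The sentence opens by referring to the primary outcome, section 2.2 dates that outcome at 6 months, and week-24 culture is scheduled for everyone. No sentence in section 6.4 says week 96; that date comes from the timeline label. This stands as a plausible account of what was intended. It does not rescue the text, because the protocol uses distinct labels for the end of treatment and the end of the trial, and section 6.4 names no other time. It does limit the point: the stated analysis needs correcting, and no data have been lost.

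**Left to the analysis plan.** Section 6.5 says that an analytical plan will be finalised before analysis. That would answer a gap, but here the protocol states a time point that conflicts with its own outcome and schedule.

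**A stronger reading to resist.** A reader might infer that a table of culture positive against culture negative drops deaths, losses and withdrawals, so that the primary analysis uses completers only. One could set about 50 dropouts per arm (498 × 10%) against about 18 expected non-cures (448 × 4%) and call the loss decisive. The document does not support this. Section 6.4 promises an intention-to-treat analysis and an outcome for each subject, and section 3.2 (Study withdrawals) keeps those who withdraw or are lost in that set. How a missing week-24 culture is classified is ordinary analysis-plan content. Nor is counting every such patient as not cured a free correction. Step 6 of the working shows its possible cost in power, and it would also score as failures the patients withdrawn because their culture proved negative, put at 1-5% of newly diagnosed cases in section 3.2.

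**Conclusion.** The point holds as a contradiction in the stated primary analysis. Section 6.4 and section 2.2 give different time points for the same outcome, and the test read literally could not produce the primary result. That conclusion rests on the protocol's own labels and culture schedule and needs no assumed figure. The 4 to 45 cultured patients per arm are illustrative: they depend on an assumed 1% to 10% smear-positive share at week 96 and on the literal reading.

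The primary result remains recoverable from the week-24 cultures, and the sample size of 498 per arm is unaffected by the correction of the time point. The conflict between sections 2.2 and 3.6 over whether smear-defined failure bars a patient from cure is separate, and remains after the date is corrected. The protocol does not state that patients without a culture are excluded, and no such claim is made here.

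**What to change.** 1. In section 6.4, replace the sentence on the primary test with wording such as: *The primary analysis compares the proportion of patients cured versus not cured at week 24 (end of treatment) between the randomised groups, in the intention-to-treat and per-protocol sets. Data from week 24 to week 96 are used only for the relapse outcome.*
2. Reconcile section 2.2 (negative culture and no smear-defined failure) with section 3.6 (culture result alone), so that one definition of cure applies, and have section 6.4 refer to it.
3. Leave the classification of patients without a week-24 culture to the analysis plan, fixed before the analysis begins. If they are to count as not cured, recheck the 96% cure assumption and the 90% power first, and say how patients withdrawn for a negative baseline culture are treated.

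Items 1 and 2 cost a few sentences and no extra visits or tests, since week-24 culture is already scheduled for all patients. Item 3 costs nothing unless missing results are counted as not cured; on the assumptions shown, power at 498 per arm would then be about 58%.

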# 4. STATISTICAL CONSIDERATIONS

The objective of the study is to demonstrate that FDCs have equivalent efficacy to the loose formulations.

Sample sizes of 498 from the intervention group and 498 from the standard group achieve 90%

power at a 5% significance level using a one-sided equivalence test of proportions when the

proportion of patients cured in the comparator group (Ps) is 96% and the maximum allowable difference (clinically acceptable difference) between proportions in the two treatment groups that still results in equivalence (the range of equivalence) is 4%. A sample size of 498 in each group is estimated with dropout rates of 10%. Two study sites will conduct the trial and contribute to the total sample size. Ethiopia will contribute a total of 498 subjects (249 in each arm) per country to reach the sample size of 996.

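### The one-sided 5% margin test on which section 4 sizes the trial is not carried into section 6.4, which gives cure a non-directional chi-square under a general alpha of 0.05

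*Protocol*

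**What the plan says.** Protocol section 4 (Statistical considerations) sets the goal of showing that FDCs are as efficacious as loose drugs. It claims 90% "power at a 5% significance level using a one-sided equivalence test of proportions". The inputs are a comparator cure rate of 96%, an allowable difference of 4 points, and 498 patients per arm, a number that already contains the allowance for loss: "A sample size of 498 in each group is estimated with dropout rates of 10"%.

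Protocol section 6.4 (Data analysis) fixes the test for that outcome: "For primary outcome Chi-square will be used to compare proportions of culture positive and culture negative subjects". It then sets one error level for everything: "In the whole analysis, an alpha of 0.05 will set the significance level for testing the null hypothesis". Section 6.4 mentions no margin, no one-sided test and no confidence interval, and it does not exempt the cure comparison from the general sentence.

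Section 6.5 says that the analytical plan will be settled before the analysis phase begins.

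**The concern.** A one-sided 5% margin test puts the whole 5% in the direction of FDC being worse. In practice it asks whether the lower limit of a 90% interval for the cure difference lies above −4 points. A two-group chi-square at 0.05 is non-directional and leaves 2.5% on each side, which corresponds to a 95% interval. A statistician who follows section 6.4 but correctly brings in the 4-point margin would therefore naturally use the 95% interval. One who follows section 4 would use the 90% interval.

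The wider interval is harder to pass, so a trial of a truly equal FDC could meet the aim under one section and miss it under the other. The 90% power in section 4 holds only at the one-sided 5% level, and section 6.4 does not secure that level.

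**Working it through.** **Inputs.** All are from section 4: 96% cure in the comparator arm, margin 0.04, one-sided 5%, 90% power, 498 per arm including 10% dropout. Section 4 gives no separate FDC cure rate, so I assume 96% in both arms. Evaluable patients per arm: 498 × 0.90 = 448.2, taken as 448.

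**Step 1: reproduce 498.** The protocol does not name its formula. I tried the Farrington-Manning score method:

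n = [z(1−α)·√V0 + z(0.90)·√V1]² / 0.04²

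- V1 (variance if the arms are equal) = 2 × 0.96 × 0.04 = 0.0768, √V1 = 0.2771.
- V0 (variance at the margin) uses the constrained estimates 0.972 and 0.932: 0.972 × 0.028 + 0.932 × 0.068 = 0.0906, √V0 = 0.3009.
- One-sided 5%: (1.645 × 0.3009 + 1.282 × 0.2771)² / 0.0016 = 452 per arm after rounding up.
- Dropout: 452 × 1.10 = 497.2, rounded up to **498**. This matches the protocol.

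Other versions do not give 498. Before dropout, the unpooled (Wald) formula needs 412, two one-sided tests need 520, and the score method at one-sided 2.5% needs 559. The sample size therefore does rest on one-sided 5%.

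**Step 2: power of the margin test at each level.**

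Score: power = Φ{[0.04·√n − z(1−α)·√V0] / √V1}

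Wald: power = Φ{0.04·√n / √V1 − z(1−α)}

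Example (score, n = 448, one-sided 2.5%): (0.04 × 21.166 − 1.960 × 0.3009) / 0.2771 = 0.927, and Φ(0.927) = 0.823.

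| Patients per arm | Method | One-sided 5% (90% interval) | One-sided 2.5% (95% interval) |
| --- | --- | --- | --- |
| 448 | Score | 89.8% | 82.3% |
| 448 | Wald | 92.1% | 86.3% |
| 498 | Score | 92.4% | 86.3% |
| 498 | Wald | 94.3% | 89.6% |

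The 498 rows apply if everyone stays in the intention-to-treat set with cure still at 96%.

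**Step 3: how often the choice of level decides the result.** A trial that passes at 2.5% also passes at 5%, so the two levels disagree in a share of trials equal to the difference in power. For a truly equal FDC at 448 per arm this is 89.8 − 82.3 = 7.5% of trials (score) or 92.1 − 86.3 = 5.8% (Wald).

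**Step 4: what these figures are not.** The chi-square in section 6.4 tests equality and has no margin. With equal true rates it is non-significant about 95% of the time, and that does not show equivalence. Its power to detect 96% against 92% is about 71% at 448 per arm. Neither number is comparable with the 90% in section 4.

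**The case against.** The strongest reply is that the protocol states one alpha, not two. Section 4 says 5% and section 6.4 says 0.05; a one-sided margin test at 0.05 satisfies both sentences literally, and section 6.4 never mentions two-sided testing or 2.5%. This stands as far as it goes: there is no numerical contradiction, and two-sidedness is inferred from the named test. But that chi-square is the only test section 6.4 gives for cure, and it has no direction, so the sizing level is still not carried over.

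Second, a reader might infer that the trial as planned has only 82–86% power. The documents do not support that. Those figures combine the margin of section 4 with the usual sidedness of the test in section 6.4, and neither section specifies that combination. Nor is 82–86% a single drop from 90%. Like for like at 448 per arm it is 89.8% to 82.3% by score, or 92.1% to 86.3% by Wald. Section 3.2 also keeps withdrawn and lost patients in the intention-to-treat set, where power at 2.5% could be 86–90%.

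Third, sidedness and interval level are commonly left to an analysis plan. Section 6.5 promises one before analysis, and section 3.3 blinds those analysing the data. So it should not be said that the level will be picked with results in view. The point survives because section 6.4 is not silent: it fixes a test and a level that do not match the sizing, and a later plan would have to depart from them.

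Finally, one might object that 5% is too lenient a risk of accepting an FDC truly 4 points worse. That is a preference. Section 4 declares the 5% openly, and nothing in the protocol promises 2.5%.

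**Conclusion.** The point holds as a mismatch between sizing and analysis. The 498 per arm and 90% power reproduce at a one-sided 5% level, and section 6.4 replaces that test with a non-directional one under a general 0.05.

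The cost is conditional. If the margin were judged with a 95% interval, power by the method that reproduces 498 would be about 82% with 448 evaluable per arm or about 86% with all 498; by Wald, 86% and 90%. This assumes 96% cure in both arms and the 4-point margin. The figures for 498 further assume that keeping lost patients in the set does not lower the cure rate. If the 90% interval is used as sized, no power is lost. The documents do not show that the trial is underpowered, nor that they set two different alphas. The wording should be corrected, but the design is not at fault.

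**What to change.** In section 6.4, replace the chi-square for the primary cure comparison with a statement that the lower confidence limit of the cure difference (FDC minus loose) is compared with −4 points at one-sided 5%, that is, the lower limit of a 90% interval. State that the general alpha sentence does not apply to this comparison. The interval formula can be left to the analytical plan.

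If two-sided 0.05 (95% interval) is intended instead, say so in both sections and restate the power in section 4 as about 82% (448 evaluable per arm) to 86% (all 498) by the score method.

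The first option costs one sentence and keeps the stated power. The second costs one restated figure, which is less favourable. Neither changes enrolment.
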